### Statistical analysis

The analysis of the primary and secondary endpoints will be performed according to the intention-to-treat principle (ITT). There will be no interim analysis. The ITT analysis population will include all randomized participants who have a valid baseline and at least one valid post baseline wound assessment (examination). For the ITT analysis population, participants will be assigned to the treatment group based on the randomization schedule, regardless of the treatment actually received. As a secondary approach a per protocol (PP) analysis will be performed excluding patients with any serious protocol deviations and changes of wound treatment. The rates of wound closure will be compared using Fisher’s exact test and time to complete closure will be compared using the Log-rank test. Safety data will be presented on an ‘as treated’ basis where patients will be grouped according to the exact wound treatment performed. Safety and secondary endpoints will be analyzed using conventional univariate testing. For the analysis of the primary efficacy endpoint missing values will be incorporated as censored values.

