
### Aim of the DiaFu study

This RCT is designed to prove that NPWT therapy leads more frequent and earlier to complete healing of diabetic foot wounds as compared to conventional moist wound therapy. Furthermore, it aims to show that NPWT therapy is also safe and effective when provided in an ambulatory care setting and to prove its overall cost-effectiveness. This trial is designed to comply with all quality requirements (randomized trial, low potential for bias; see Discussion section) of IQWiG and G-BA, as well as other European authorities.

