## Methods/Design

The DiaFu study is designed as a national, multicenter, randomized controlled clinical superiority trial across Germany, with blinded photographic analysis of the primary endpoint. Participants are randomly allocated in a 1:1 ratio to each treatment group. Allocation to treatment groups is performed using a centralized web-based tool. To ensure good balance of participant characteristics in each group a stratified randomization is performed. Participants are stratified by study centre and by Wagner-Armstrong stage within each centre (<Wagner-Armstrong stage 2C and ≥ Wagner-Armstrong stage 2C; Figure 1). Due to the physical differences between the treatment regimens it is not possible to blind either participant or physician to the treatment arm. To address issues of blinding, confirmation of wound closure will be assessed via blinded assessment of wound photographs by independent observers.

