### Primary and secondary endpoints

Time until complete (100% epithelization) wound closure and the number of wound closures in each treatment group achieved in the maximum study treatment time of 16 weeks (112 days) are the primary endpoints of the DiaFu study. Complete wound closure is defined by 100% epithelialization of the wound (no granulation tissue visible), no drainage, no sewing material and no need for wound dressing or adjuvants. The assessment of complete wound closure is primarily based on the central blinded review of photographs performed by independent analyzers. Complete wound closure can be achieved either by surgery or by secondary intention. However, surgical intervention (for example wound suture, skin grafting or flap transplantation) is allowed only if the wound bed is prepared adequately. Sustainment of complete wound closure has to be proven by a satisfactory follow-up examination of the area 14 days after the intervention (wound closure verification visit). If the wound cannot be closed before the end of the maximum treatment time of 16 weeks, a study visit to assess the wound status and for evaluation of the secondary endpoints is performed.

Secondary clinical endpoints are the time until complete wound closure within the study time of six months, the number of wound closures per treatment group achieved within six months, the time until optimal preparation of the wound bed for further treatment (a minimum of 95% granulation), recurrences, amputations with incidence and extent, the wound size over time (area of wound opening, maximal length and width (cm^2^)) and the composition of wound tissue (percentage of epithelial layer, granulation tissue and fibrin).

The incidence of serious adverse events (SAEs) including mortality of any cause within six months from the time of initiation of therapy, incidence of device-related adverse events (ADEs) and incidence of wound-related adverse events (AEs) occurring within the study treatment time of 16 weeks or until wound closure confirmation are considered to be safety endpoints of this trial.

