### Avoiding potential bias

Within the reports of the IQWiG and the updated systematic literature review of Peinemann and Sauerland [14] the risk of bias within the considered trials was examined using the predefined criteria shown in Table 2. All five criteria had to be met for the potential for bias to be described as low. The DiaFu- study is designed with the aim of avoiding all potential bias.

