**Table 2 Tab2:** **Potential bias**

Criteria for potential bias	Explanation
RCT	The performance of a randomized controlled trial is required.
Suitable allocation to groups	A precise description of the randomization sequence generating procedure is required (such as computer-generated lists).
Allocation to groups suitably concealed	Information on how allocation to groups is blinded is required (for example centrally by telephone or using sealed opaque envelopes).
Assessment of endpoints blinded	Information on who (patient and/or researcher) assessed which endpoint under blinding conditions (without knowing the group to which the patient had been allocated) is required.
Reasons given for any data loss	The requirement is either no data loss or, if data loss is reported, identification of all patients whose data could not be fully evaluated after randomization and the reasons for this (for example patients who dropped out before the beginning of treatment or during follow-up).
Adequate ITT analysis	Evaluation using the number of randomized patients as the size of the population is required

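### The set labelled ITT leaves out randomised patients without a valid post-baseline wound assessment, which conflicts with the article's own bias criterion and exposes both primary endpoints to a possible exclusion bias

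*Protocol article*

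**What the plan says.** The Statistical analysis section of the protocol article states: "The analysis of the primary and secondary endpoints will be performed according to the intention-to-treat principle (ITT"). It then defines the set: "The ITT analysis population will include all randomized participants who have a valid baseline and at least one valid post baseline wound assessment (examination"). Patients in this set are kept in their randomised group whatever treatment they received. The only other efficacy set described is the per-protocol set, which is smaller still. Missing values for the primary efficacy endpoint are to be treated as censored. Closure rates are compared with Fisher's exact test and time to closure with the log-rank test.

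Under Avoiding potential bias, Table 2 lists the criteria by which earlier NPWT trials were graded. Its entry for adequate ITT analysis reads: "Evaluation using the number of randomized patients as the size of the population is required". The text above the table adds: "All five criteria had to be met for the potential for bias to be described as low". The Aim section applies the standard to this trial: "This trial is designed to comply with all quality requirements (randomized trial, low potential for bias; see Discussion section) of IQWiG and G-BA". The Abstract repeats that commitment.

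The Methods/Design section says that "it is not possible to blind either participant or physician to the treatment arm".

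**The concern.** Two statements about the same analysis do not agree. One makes the analysed population depend on having been examined after randomisation; the other requires it to equal the number randomised. As soon as one randomised patient has no valid post-baseline assessment, the planned primary analysis misses a criterion that the article says the trial is designed to meet. That matters because the trial is meant to inform a reimbursement decision after earlier evidence was judged uncertain.

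There is also a statistical risk. Having a post-baseline assessment is an outcome of the trial, not a baseline characteristic. Patients and physicians know the allocation, so the chance of never being assessed could differ by arm, and those never assessed could have a different prognosis from those who stay. If both happen, the comparison is no longer the randomised one. Blinded photograph review does not protect against this, because a patient who is never assessed supplies no photograph to review. Both primary endpoints use the same set.

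**Working it through.** **1. The two rules side by side.**
- Statistical analysis: N analysed = N randomised − (no valid baseline) − (no valid post-baseline assessment).
- Table 2: N analysed = N randomised.
- They agree only if both subtractions are zero. The second condition is the one that arises after randomisation.

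**2. The stated sample size.** Inputs from Power calculation: 45% and 30%, α = 0.05 (two-sided reproduces the figure), power 80%. With pooled variance, p̄ = 0.375:

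n = [1.960·√(2·0.375·0.625) + 0.842·√(0.45·0.55 + 0.30·0.70)]² / 0.15² = (1.342 + 0.569)² / 0.0225 ≈ 162.3.

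This matches the stated 162 per group (163 if rounded up; the unpooled variant gives 160). The concern does not depend on this figure. It does show that 162 contains no allowance for excluded patients.

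**3. Effect on the observed difference at the planning rates.** Assumption: 10% of one arm (16 patients) is excluded and all are non-closers. Planned closures are about 73 of 162 and 49 of 162.
- No exclusion: 45.1% − 30.2% = 14.8 points.
- 16 excluded from NPWT: 73/146 = 50.0%; 50.0% − 30.2% = 19.8 points.
- 16 excluded from control: 49/146 = 33.6%; 45.1% − 33.6% = 11.5 points.

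The planned difference of 15 points therefore moves to about 20 or 11.5, depending on which arm loses patients.

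**4. Type I error of Fisher's test.** Assumptions: true closure rate 30% in both arms, 162 randomised per arm, *k* non-closers excluded, and the remaining closures binomial with rate 0.30·162/(162 − *k*) = 48.6/(162 − *k*). Two-sided rejection probabilities come from full enumeration.

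| Excluded, NPWT / control | Apparent rates | Rejection at 0.05 | Rejection at 0.025 |
|---|---|---|---|
| 0 / 0 | 30.0% / 30.0% | 3.7% | 1.9% |
| 8 (5%) / 0 | 31.6% / 30.0% | 5.3% | 2.7% |
| 16 (10%) / 0 | 33.3% / 30.0% | 8.3% | 4.8% |
| 24 (15%) / 0 | 35.2% / 30.0% | 14.6% | 9.2% |
| 16 (10%) / 16 (10%) | 33.3% / 33.3% | 3.8% | 1.8% |

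The 0.025 column is the first Bonferroni-Holm step. Using exact fractions, 0.30/(1 − loss), instead of whole patients gives 8.5% and 14.9% in place of 8.3% and 14.6%.

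**5. Time to closure.** The log-rank numerator is the sum over closure times of d₁ − d·n₁/n, where n and n₁ count patients still at risk. A patient censored at day 0 is in no risk set and adds nothing, so censoring at day 0 and excluding give the same statistic. A simulation confirmed this (2,000 runs per scenario, 162 per arm, 30% closure by day 112 in both arms, non-closers removed from NPWT only):

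| Excluded from NPWT | Excluded, or censored at day 0 | Kept as not closed to day 112 |
|---|---|---|
| 5% | 6.5% | 5.0% |
| 10% | 9.2% | 5.0% |
| 15% | 15.2% | 4.4% |

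The simulation error near 5% is about √(0.05·0.95/2000) = 0.5 points.

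**The case against.** The strongest reply is that the bias is not shown. The article gives no exclusion rate, no difference by arm and no date for the first post-baseline visit. The rule asks for only one valid examination, so few patients may be affected. The scenarios above are one-sided and take every excluded patient as a non-closer. Equal exclusion does not inflate the error, and even a wholly one-sided 5% loss gives 5.3%, close to nominal. All of this stands, and it is why the bias is stated as a risk.

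Three stronger readings are tempting, and the document does not support them:
- A reader might infer that refusing the pump, early bleeding or amputation removes a patient from the analysis. It does not by itself. Patients stay in their allocated group whatever they received, amputation is a recorded endpoint, and serious adverse events including death are followed for six months. Only a patient with no valid wound assessment afterwards is excluded.
- A reader might infer that the exclusions will depend on the arm and favour NPWT. Lack of blinding makes arm dependence possible, not established, and step 3 shows that the shift can go either way.
- A reader might infer that the trial is bound to fail the criterion of the bodies that commissioned it. Failure needs at least one exclusion. The statutory health insurers initiated the trial; IQWiG and G-BA appear as assessor and decision-maker.

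Other replies carry less weight. Table 2's data-loss entry accepts losses with stated reasons, but it does not waive the separate ITT entry. Modified ITT sets are common, but this article sets the stricter standard and keeps the label ITT. An analysis plan may add analyses of all randomised patients, but the primary set is fixed here and a different set there would contradict this text.

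**Conclusion.** The inconsistency is certain: the set defined under Statistical analysis is a modified ITT set, and it breaches the Table 2 criterion whenever one randomised patient is excluded. The bias is conditional. It needs exclusions that differ by arm and relate to outcome, which is possible in an unblinded trial.

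If exclusions fall in one arm only and only on non-closers, the effect is small at 5% but clear at 10% to 15%: error rates of roughly 8% to 15% on either primary endpoint at the nominal 0.05 level, and at 10% a shift of about 3 to 5 points in a planned 15-point difference. If exclusions are equal by arm, the type I error is not inflated, although both closure rates are overstated when only non-closers are lost. All exclusion rates here are assumptions.

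The text should be corrected before analysis, because the criterion is the article's own and the repair is cheap.

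**What to change.** 1. Define the primary analysis set as all randomised patients in their allocated arm, with time zero at randomisation.
2. For the 16-week closure rate (Fisher's test), count patients without any post-baseline assessment as not closed.
3. For time to closure, carry these patients as not closed to day 112, at least as a stated sensitivity analysis. Re-admitting them under the present censoring rule, in effect at day 0, would change nothing in the log-rank test.
4. Keep the present set as a sensitivity analysis, renamed modified ITT, and report exclusions by arm with reasons.

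Cost: a few sentences in the analysis section and no new data. The figure of 162 per group stands if the planning rates are read as rates among all randomised patients. Closure rates become slightly more conservative. Counting unassessed patients as not closed is a single imputation and may understate healing among those who leave early, including in one arm more than the other; the modified ITT result beside it shows how much depends on that choice.

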### Power calculation

The superiority hypothesis is tested in parallel with two different outcomes for the rate of wound closure and the time to wound closure in a fixed maximum treatment period of 16 weeks. The method of Bonferroni-Holm will be used for the adjustment of the α-error for parallel confirmatory testing of both primary endpoints. This means that after testing for both endpoints the smaller P value has to be <0.025 while the other has to be <0.05 for statistical significance. The sample size calculation is based primarily on the difference between wound closure rates in both treatment arms. The expected difference of the wound closure rates is based on information extracted from published previous studies. Armstrong and Lavery [16] described a rate of complete wound closure within 56% of patients with NPWT and within 39% of patients in the corresponding control group. Blume [17] showed a rate of complete wound closure within 43% of patients treated with NPWT and 29% of patients in the control group. For the present study success rates for achieving of the primary endpoint of 45% for NPWT and 30% in the control group are assumed, resulting in an absolute difference of at least 15% in the rate of complete wound closure results. Based on a type one error of α = 0.05 and a type two error of β = 0.2 (corresponding to a power of 80%) a total sample size of 162 patients per group (324 in total) is needed to prove the primary endpoint (wound closure rate).

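### Randomisation is stratified by centre and wound stage, but both primary tests are named without strata: type I error stays controlled, and a few points of power are forgone

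*Protocol article*

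**What the plan says.** The Methods/Design section gives the allocation scheme: "Participants are stratified by study centre and by Wagner-Armstrong stage within each centre". Stage is split at 2C, and the purpose is stated: "To ensure good balance of participant characteristics in each group a stratified randomization is performed".

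The Statistical analysis section then sets the two primary comparisons. Closure rates are compared with Fisher's "exact test and time to complete closure will be compared using the Log-rank test". No stratum or covariate is named for either test.

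The Power calculation section rests on the closure rate alone: "success rates for achieving of the primary endpoint of 45% for NPWT and 30% in the control group are assumed". It continues: "Based on a type one error of α = 0.05 and a type two error of β = 0.2", and concludes that "a total sample size of 162 patients per group (324 in total) is needed". Strata do not enter this calculation. Under Bonferroni-Holm, "the smaller P value has to be <0.025 while the other has to be <0.05".

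**The concern.** Balancing the arms within prognostic strata removes part of the chance variation in the treatment difference. A test that pools all patients into one table or one risk set still allows for that variation. Its reference distribution is then too wide: the true type I error falls below nominal and some real effects are missed. The error is on the safe side, so what is at stake is power and precision. These matter here because the trial is meant to inform a reimbursement decision and has no interim analysis.

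**Working it through.** **Inputs from the protocol article.** Closure 45% and 30%, 162 per arm, 1:1 allocation, α 0.05, power 80%. The article does not state whether α is one- or two-sided, but the sample size fits two-sided.

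**Assumed inputs.** The article gives no prognostic strength for stage or centre, and its list of sites is in a figure that is not shown. These values are therefore assumptions, given as ranges.

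**1. The plan's own figure.** Mean rate (0.45 + 0.30)/2 = 0.375.
- Pooled normal formula: n = [1.960·√(2·0.375·0.625) + 0.842·√(0.45·0.55 + 0.30·0.70)]² / 0.15² = (1.342 + 0.569)² / 0.0225 = 162.3, so 163 per arm.
- Arcsine formula: n = (1.960 + 0.842)² / [2·(arcsin√0.45 − arcsin√0.30)²] = 7.849 / (2·0.1557²) = 161.9, so 162 per arm.

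The stated 162 reproduces, without any use of strata.

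**2. The named test at that size.** Enumerating all tables at 162 per arm, Fisher's test has power 76.5% at 0.05 and 67.4% at 0.025. Its true size at nominal 5% is about 3.7% to 3.8% when both rates are 30%. None of this involves strata; it comes from the discreteness of the exact test.

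**3. What ignoring stage does by itself.** Take two equal stage strata and a common closure rate of 30%.
- With a log-odds ratio of 0.8, the stratum rates are about 21.8% and 38.2%. The mean within-stratum variance is (0.218·0.782 + 0.382·0.618)/2 = 0.203, where an unstratified test assumes 0.30·0.70 = 0.21. The ratio is 0.968, the effective critical value 1.96/√0.968 = 1.992, and the size 4.6%.
- With a log-odds ratio of 1.1, the rates are about 18.9% and 41.1%, the variance 0.198, the ratio 0.941, the critical value 2.020 and the size 4.3%.

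**4. Simulation by stage** (100,000 trials, 81 per arm per stratum, log-odds ratio 0.8 to 1.1). Pearson's unstratified test is included to separate the two sources of loss.

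| Test | Power | True size |
|---|---|---|
| Fisher | about 77% | 3.2–3.5% |
| Pearson, unstratified | about 80% | 4.3–4.6% |
| CMH by stage, no continuity correction | 81.6–82.6% | 5.0–5.1% |

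Fisher to Pearson is about 3.2 points, from discreteness. Pearson to CMH is about 1.4 to 2.1 points, from the strata. Pearson's size agrees with step 3. With a continuity correction, CMH power is only 78.3% to 79.3%, so most of the gain over Fisher goes.

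**5. Adding centre** (10,000 trials; centre SD on the logit scale). Power at 0.05, with size in brackets, in %:

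| Assumed strata | Fisher | Pearson | CMH by stage | CMH by centre and stage |
|---|---|---|---|---|
| None, 40 centres | 78.4 (4.5) | 80.8 (5.4) | 80.8 (5.4) | 80.7 (5.3) |
| Stage OR 2, centre SD 0.5, 20 centres | 78.7 (3.6) | 81.1 (4.2) | 81.9 (4.3) | 83.1 (5.0) |
| Stage OR 4, centre SD 1, 20 centres | 80.1 (2.0) | 82.4 (2.5) | 84.6 (3.2) | 88.3 (4.8) |

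These runs put Fisher slightly above the exact 76.5% even without strata effects, so read the differences between tests and not the levels. The strata are worth about nothing in the first row, 83.1 − 81.1 = 2.0 points in the second and 88.3 − 82.4 = 5.9 in the third.

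**6. Log-rank test** (20 centres, 1,500 trials; Monte Carlo error of a power near 82% is √(0.82·0.18/1500), about 1 point). Power at 0.05, with size in brackets, in %:

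| Assumed strata | Unstratified | By stage | By centre and stage |
|---|---|---|---|
| None | 80.9 (5.4) | 80.7 (5.5) | 79.1 (5.2) |
| Stage HR 2, centre SD 0.5 | 82.1 (4.1) | 83.8 (4.7) | 82.7 (5.0) |
| Stage HR 4, centre SD 1 | 86.0 (1.4) | 89.7 (1.9) | 95.1 (4.1) |

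A separate stage-only run gave a gain of about 2 to 2.6 points under the effects assumed in step 4, and none without them. Full centre-by-stage stratification costs about 2 points (80.9 − 79.1 = 1.8) when the strata are not prognostic.

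**The case against.** The strongest objection is about attribution. Setting Fisher against CMH compares an exact test with an asymptotic one, and a reader might infer that the whole gap of 4 to 5 points comes from ignoring the strata. It does not. Without any strata effect Pearson and CMH have equal power, and roughly 3 points of the gap remain because Fisher is discrete. This objection stands, and the sizes given here are split accordingly.

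It can also be said that an analysis plan not shown may stratify the log-rank test, since that test is named without a qualifier. This stands for the log-rank test. It does not stand for the closure rate: Fisher's exact test is by construction a test of one unstratified table, so that choice is fixed.

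A third objection is that nothing planned is lost, because the 162 per arm took no credit for stratification. That also stands. The strata part is efficiency forgone and not an error in the sample size. Whether Fisher and the Holm threshold fit the stated 80% is a separate matter.

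A reader might go further and infer that baseline wound area has to be in the primary model, or that wound area over time will be analysed without its baseline. The article supports neither. Wound area is not a stratification factor, and "Safety and secondary endpoints will be analyzed using conventional univariate testing" does not exclude a test on change from baseline.

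**Conclusion.** The mismatch between allocation and analysis is in the text, and its direction is clear: both primary tests are conservative if stage or centre is prognostic. A reader might infer an inflated type I error or an invalid analysis; the calculations show the opposite, with size at or below about 5%.

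For the closure rate, a stage-stratified CMH test without continuity correction would have about 82% power against about 77% for Fisher, if the stage log-odds ratio is 0.8 to 1.1. Of that, 1.4 to 2.1 points are due to stratifying. The strata part grows if centres differ and vanishes if neither factor matters. For the log-rank test the gain is about 1 to 3 points with moderate strata, close to simulation error. The direction is certain, but the size rests on assumed prognostic strength. This is a worthwhile efficiency change, not a correction of an invalid test.

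**What to change.** Name as primary tests a CMH test without continuity correction for the closure rate and a stratified log-rank test for time to closure. Stratify both by the stage stratum used at randomisation (below 2C against 2C or above). Pool small centres, or handle centre in a supporting model, so that sparse centre-by-stage cells do not cost the log-rank test power. Keep unstratified Fisher and log-rank as sensitivity analyses.

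The change is to analysis wording only and needs no new patients, visits or data, since stage and centre are already recorded for allocation. It must be made before database lock. The small downside is that the closure-rate test becomes asymptotic instead of exact; its simulated size by stage was 5.0% to 5.1%.

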### Intervention and control

In the intervention group medical devices using the principle of NPWT will be applied on the study wound [7, 8]. This therapeutic technique uses a vacuum dressing to promote healing. The therapy involves the controlled application of sub-atmospheric pressure to the local wound environment, using a sealed wound dressing connected to a vacuum pump. NPWT promotes wound healing through optimization of blood flow, decreasing local tissue edema and removing excessive fluid from the wound bed. These physiologic changes facilitate the removal of bacteria from the wound. Additionally, the cyclical application of sub-atmospheric pressure alters the cytoskeleton of the cells in the wound bed through microstrain, triggering a cascade of intracellular signals that increase the rate of cell division and subsequent formation of granulation tissue. Moreover, this system has been shown to also cause macrostrain, bringing the edges of the wound closer and also stimulating wound bed granulation. NPWT as interim therapy should be discontinued once the condition of a wound is suitable for closing, either spontaneously or surgically.

Table 1 gives an overview of the NPWT devices used within the trial. Medical devices used within the trial are all CE certified products. All NPWT devices and dressings to be utilized in this study bear the CE mark and will be operated within normal conditions of use and according to clinical and manufacturers guidelines. Dressing changes are recommended to be performed according to manufacturer’s instructions with frequency adjusted by the clinician as appropriate. Contraindications and precautions will be noted.

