**Dressing**	
V.A.C^.®^ Granufoam^®^ (black)	Foam dressing (RENASYS^TM^ –F/P)
V.A.C^.®^ Granufoam^®^ silver^®^	Gauze dressing (RENASYS^TM^ –G)
V.A.C.^®^ Whitefoam^®^	

The table shows the NPWT devices of Kinetic Concepts Incorporated (KCI) and Smith & nephew used within the trial.

Control therapy is defined as any conventional moist wound therapy according to local clinical standards and guidelines [6]. Healthcare providers are obligated to provide patients with best practice and standard of care. In the control arm it is permitted to apply every local wound treatment standard used in the respective study site that does not have an experimental status or is based on the principle of NPWT.

To ensure the quality of local wound treatment during the course of the study, the study sites are trained for both the intervention arm and the control arm. The manufacturers are responsible for the training with the NPWT systems and consumables (dressing materials). The German Society for Wound Healing and Wound Treatment (German: Deutsche Gesellschaft für Wundheilung und Wundbehandlung e.V.) provides parts of their curriculum and performs the training for the control arm.

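### Device-related adverse events fall under the blanket rule for univariate testing, but if the device is the NPWT system, patients treated only with moist therapy cannot have one

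*Protocol article*

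**What the plan says.** **Endpoint.** Under Primary and secondary endpoints, the protocol article names serious adverse events including mortality (six months) and then "incidence of device-related adverse events (ADEs) and incidence of wound-related adverse events (AEs) occurring within the study treatment time of 16 weeks", or until closure is confirmed, as the safety endpoints.

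**Analysis.** Under Statistical analysis, safety data are presented as treated: "patients will be grouped according to the exact wound treatment performed". The next sentence reads "Safety and secondary endpoints will be analyzed using conventional univariate testing". No safety endpoint is exempted, and no particular test is named for safety.

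**Device.** Under Intervention and control, "In the intervention group medical devices using the principle of NPWT will be applied on the study wound". The legend of Table 1 says "The table shows the NPWT devices of Kinetic Concepts Incorporated (KCI) and Smith & nephew used within the trial", and the table lists only these systems and their dressings. Phase and classification of the trial refers to the investigational devices as CE-marked. The Abstract uses the CE mark for the treatment systems of the intervention group. Control therapy is moist wound care by local standard, and treatment based on NPWT is ruled out.

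**The concern.** A between-group test of incidence is informative only if the event can occur in both groups. If an ADE is an event related to the NPWT system, a patient who never had NPWT cannot have one. Equality of the two incidences is then excluded by design as soon as NPWT causes any ADE at all. The p-value depends only on how many NPWT patients had an event and on the group sizes.

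The aim of the study includes showing that NPWT is safe in ambulatory care, and the results are meant to inform a reimbursement decision. A significant ADE test could be taken as evidence of excess harm, although comparable events under moist therapy are not counted. A non-significant one could be taken as reassurance. Neither inference would be valid.

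**Working it through.** **1. Does the plan call for the test?** The endpoint list contains ADE incidence. The analysis sentence covers safety endpoints as a class, and it follows directly on the sentence that forms as-treated groups. Taken together, the natural reading is a test between treatment groups that includes ADEs.

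**2. Is the moist-only count zero by design?** The trial's listed medical products are NPWT systems and their dressings, and control treatment may not be based on NPWT. As-treated grouping makes the zero firmer, because a control patient who receives NPWT no longer belongs to a moist-only group. The zero is structural if *device* means the NPWT system.

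**3. Group size used for illustration.** The Power calculation section gives 162 per group for closure rates of 45% and 30%, α = 0.05 and 80% power. Check with the two-sided formula and no continuity correction:

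n = [1.96 × √(2 × 0.375 × 0.625) + 0.8416 × √(0.45 × 0.55 + 0.30 × 0.70)]² / 0.15²

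= (1.342 + 0.569)² / 0.0225 ≈ 162.3, that is 163 when rounded up.

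The stated figure is reproduced to within one patient. It was not derived for safety and serves here only as a group size.

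**4. What the p-value does against a fixed zero.** Fisher's test is an assumption, since the article names it only for closure rates. With k of 162 against 0 of 162, the two-sided p-value is 2 × C(162, k) / C(324, k):

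| NPWT patients with an ADE | Proportion | p |
|---|---|---|
| 4 | 2.5% | 0.123 |
| 5 | 3.1% | 0.061 |
| 6 | 3.7% | 0.030 |
| 7 | 4.3% | 0.015 |
| 8 | 4.9% | 0.007 |

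The 0.05 threshold is crossed at k = 6.

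**5. How often that happens.** P(k ≥ 6) for a Binomial(162, π) count, with π the assumed ADE risk per NPWT patient (the article gives none):

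- π = 2%: 11%
- π = 3%: 36%
- π = 5%: 82%

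No property of the moist-therapy group enters these figures except its size.

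**6. What an estimate would show instead.** For 6 of 162, the exact (Clopper-Pearson) 95% interval runs from the 2.5% quantile of Beta(6, 157) to the 97.5% quantile of Beta(7, 156), which is 1.4% to 7.9%. For 5 of 162 it is 1.0% to 7.1%. The two intervals are nearly the same, although the test would call one result significant and the other not.

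**The case against.** **The ADE test is inferred.** No sentence names an ADE comparison, hypothesis or test. The inference rests on one general sentence in a condensed article, and the full protocol or analysis plan may treat ADEs descriptively. A reader might infer that the sponsor has expressly planned an ADE comparison between arms, and the text does not support that. What remains is that the article fixes a method for all safety endpoints, and for this one the method does not fit.

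**The device is not defined.** Table 1 counts dressings among the medical products, and the article refers to ISO 14155 for adverse event definitions without saying which products are meant. Events attributed to control-arm products are not expressly excluded. This stands, so the zero is conditional on the natural reading.

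**Relative safety does not rest on ADEs.** Serious adverse events, mortality and wound-related adverse events can occur in both groups and are already safety endpoints. This also stands, and it limits the severity.

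**Device-free time.** NPWT is interim: "NPWT as interim therapy should be discontinued once the condition of a wound is suitable for closing, either spontaneously or surgically". The ADE window nevertheless runs to 16 weeks or closure confirmation. A reader might infer that device-free time understates the ADE incidence. The article does not support this. It plans an incidence, and a longer window cannot lower the proportion of patients with an event. No rate per unit of time is planned, no wear time is given, and nothing says that device events arise only during wear.

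**Conclusion.** The point holds as a minor one. If *device* means the NPWT system and the general testing sentence is applied to ADEs as written, the comparison is against a structural zero and its p-value carries no information on relative safety. At 162 per group, the result moves from p = 0.061 to p = 0.030 with a single further NPWT patient (5 to 6), whatever happens under moist therapy.

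The figures are illustrative. They assume Fisher's test, as-treated groups of the planned randomized size, and the ADE risks shown. If moist dressings also counted as devices, the zero would no longer be structural, and the definition would have to be stated. The primary endpoints, the sample size and the other safety endpoints are not touched, so it would go too far to conclude that the trial's safety comparison as a whole is unsound.

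**What to change.** In the Statistical analysis section, exempt ADEs from between-group testing. State that *device* in this endpoint means the NPWT system, if that is intended. Report ADEs descriptively in patients who received NPWT, as the proportion with at least one event and its exact 95% confidence interval. A rate per device-day can be added if wear time is recorded. The article does not say that it is, so the sponsor should confirm this first.

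Keep the between-group safety comparison on serious adverse events, mortality and wound-related adverse events.

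The cost is a change of wording and the loss of one uninformative p-value. Treatment, sample size and primary analysis stay as they are.
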